** *Weeks 7–8: Transfer and Stabilization Phase* **				
**Goal:** Transferring learning to real-game situations and increasing neural flexibility				
** *Num* **	** *Exercise Name* **	** *Description* **	** *Cognitive Task Description* **	** *Repetition* **
1	Single-leg balance on a Bosu ball with knee flexed at 60°, Eyes open	The athlete balances on one leg atop a Bosu ball, with their knee flexed at approximately 60 degrees and eyes open, focused on a wall.	While positioned in front of a wall displaying multiple-colored targets, the athlete maintains balance on a single leg atop a Bosu ball. In response to verbal cues provided by a partner (e.g., “yellow”), the athlete dynamically reaches with the upper limb to touch the corresponding-colored circle. This task is designed to enhance visual discrimination, decision-making, and upper-limb coordination under postural control demands.	1 set/ 20s
2	Single-leg balance on a Bosu ball, Eyes open	While standing on one leg with knees slightly bent on a Bosu ball, the athlete maintains balance and catches a ball passed by the partner, then returns it.	During the ball-passing task, the athlete answers simple verbal questions (e.g., “What day is it today?”), engaging attention and verbal processing alongside physical stability.	1 set/ 15s
3	Stance on balance cushion, Open eyes	The athlete stands on one leg on a soft balance cushion with eyes open. Four colored cones are placed anterior, posterior, and lateral to the athlete.	Upon verbal command from the partner indicating a color, the athlete touches the corresponding cone using the free foot, integrating balance control with working memory and response execution.	1 set/ 20s
4	Lunge jump on dual steps with trunk rotation	The athlete starts between two 10 cm-high steps and performs a plyometric lunge with an explosive vertical jump, landing with each foot on a separate step while rotating the trunk.	Upon landing, the athlete receives a ball passed by the partner, requiring anticipatory timing, visuomotor coordination, and dual-task balance.	2 sets/4 reps
5	Drop landing and Barrier jump, and Rotational step landing	The athlete drops from a step to the floor, immediately jumps over a 20 cm hurdle, and lands on a secondary step while rotating the trunk 90°, resulting in a directional change of gaze.	While performing the movement, the partner verbally presents three random single-digit numbers. The athlete must calculate and announce their sum upon completion of the movement.	2 sets/5 reps
6	90°-degree medial hops	The athlete performs a single-leg hop while rotating 90° medially mid-air, landing with controlled knee flexion on the same leg. The posture is held for a minimum of 3 seconds. Direction is opposite to the stance leg (e.g., right leg initiates leftward rotation).	During execution, the athlete responds to simple verbal questions (e.g., “What color is the sky?”), maintaining cognitive engagement.	2 sets/6 reps
7	Crossover hop	From a single-leg stance, the athlete performs three consecutive crossover hops over a central line (e.g., right leg: left → right → left), maintaining balance in a deep flexion hold for at least 3 seconds on the final landing.	The partner presents three or five single-digit numbers during the movement, which the athlete must retain and recall in correct sequence after completing the task.	2 sets/6 reps
8	Multi-directional hop-hop-hold	The athlete performs two consecutive hops in a designated direction (forward, backward, left, or right) on one leg and holds the final landing position for 3 seconds.	During the task, the athlete responds to simultaneous visual cues indicating a color and a number, integrating visual processing and cognitive flexibility.	2 sets/ 10s
9	Lateral hop over barriers and step jump	The athlete stands laterally and hops over three 10 cm barriers, concluding with a vertical jump onto the elevated step.	Performs a Stroop color-naming task by stating the ink color of printed words, requiring inhibition of automatic reading.	2 sets/8 reps
10	Medial hop over barriers and step jump	The athlete stands medially and hops over three 10 cm barriers, concluding with a vertical jump onto the elevated step.	Engages in a Stroop word-reading task, reading the word itself regardless of its ink color, stimulating cognitive inhibition and selective attention.	2 sets/8 reps
11	Drop landing to maximum vertical jump	The athlete drops from a step, lands on one foot, and immediately performs a maximal vertical jump with the same leg.	The partner reads out a sequence of three single-digit numbers during the movement; the athlete recalls and states the numbers in order after completion.	2 sets/6 reps
12	Drop landing to single-leg lateral jump with reversed cue	The athlete drops from a step with one leg, then immediately performs a lateral jump to the side opposite of the instructed landing leg.	The athlete receives a landing cue from the partner (e.g., “Land on right”), but must perform the movement using the opposite foot, introducing a cognitive inhibition and reverse-reaction component.	2 sets/8 reps

In the first phase (Weeks 1–2), referred to as the Controlled Movement Phase, the primary goal was to establish proper multi-plane movement patterns and improve movement strategies associated with dynamic knee valgus through foundational exercises performed under high levels of external feedback. Training emphasized sagittal-plane movements with controlled frontal-plane components, simple single-task neuromuscular exercises accompanied by real-time verbal and visual feedback, and the introduction of basic cognitive tasks. Exercises were performed in pairs to allow peer observation and feedback, mainly on stable surfaces with bilateral support when needed, and at low to moderate intensity.

The second phase (Weeks 3–4), referred to as the Strategic Planning Phase, aimed to introduce moderate cognitive demands by emphasizing decision-making and motor planning during movement. This stage incorporated a greater proportion of single-leg exercises, integration of dual-task conditions combining motor and cognitive demands, and more complex cognitive challenges such as choice reaction time and stimulus discrimination. External feedback was reduced to encourage reliance on internal sensory feedback mechanisms, while unstable surfaces and dynamic balance challenges were introduced. Exercises were performed at moderate intensity and complexity.

In the third phase (Weeks 5–6), called the Automatic Processing Phase, the objective was to develop more efficient motor control under cognitive load and improve dual-task proficiency. Athletes received minimal external feedback and were encouraged to self-monitor and correct their performance. Training involved complex multi-directional movements across multiple planes, high cognitive load tasks requiring divided attention, and increased speed and intensity. Sport-specific movement patterns resembling volleyball actions were emphasized, with a focus on efficient and fluid movement execution.

Finally, the fourth phase (Weeks 7–8), designated as the Transfer and Stabilization Phase, sought to facilitate the transfer of acquired skills to competition-like situations, emphasizing frontal-plane single-leg control and reinforcement of learned motor adaptations. This stage involved maximum cognitive load with unpredictable, game-like stimulus conditions, frontal-plane dominant single-leg tasks mimicking volleyball-specific movements such as lateral cutting and defensive slides, and integration of volleyball equipment and scenarios. Exercises were performed at high intensity and speed, under fatigue and time pressure, to facilitate application of learned skills during dynamic sport situations.

Athletes will progress to the next training phase only when they consistently meet predefined progression criteria across three consecutive sessions. Movement quality will be assessed by a trained coach using a standardized checklist, ensuring appropriate lower-extremity alignment according to predefined movement-quality criteria. Cognitive performance will also be evaluated, requiring athletes to commit no more than three predefined cognitive errors per session during tasks involving stimulus responses or rule-based challenges. Athletes must maintain movement quality under dual-task conditions without clinically meaningful deterioration compared with single-task performance and execute tasks at the prescribed speed and intensity while meeting cognitive demands. Since progression is individualized, athletes who do not meet the criteria after completing the planned two-week phase will remain at the same level with modified or alternative exercises of similar complexity until the requirements are achieved, thereby supporting adequate motor learning, confidence development, and minimizing inappropriate progression-related injury risk. All progression decisions will be documented using standardized forms and reviewed weekly by the supervising sports rehabilitation specialist to ensure safety.

Training intensity will be indirectly quantified using the session rating of perceived exertion (session-RPE) method [23]. Approximately 30 minutes after each session, each participant will rate her perceived exertion using the modified Borg CR-10 scale; session-RPE will then be multiplied by session duration (minutes) to calculate session training load. Weekly training load will be reviewed by the supervising sports rehabilitation specialist alongside the movement-quality and cognitive-error checklists to identify unusual increases in perceived exertion and inform individualized progression decisions.

### Control group protocol

The control group will receive an active control intervention consisting of the same neuromuscular training exercises as the experimental group but performed exclusively under single-task conditions without cognitive challenges. This design will control for exercise volume, intensity, trainer attention, and social interaction, thereby estimating the additional contribution of cognitive training integration. Training will be delivered three times per week for eight weeks, with each session lasting approximately 60 minutes and following an identical structure to the experimental group: a 15-minute warm-up, 30–40 minutes of main training, and a 10-minute cool-down. Progression will follow the same four-phase structure, with gradual increases in exercise difficulty, intensity, and complexity. Instructional methods will include verbal cueing, demonstration, and corrective feedback; all will be provided with a single-task focus to ensure consistency across groups while eliminating additional cognitive demands.

Both groups will continue their regular volleyball team training sessions, competitions, and usual physical activities throughout the 8-week intervention period. All participants will be instructed to maintain consistent training and competition schedules and report any changes in activity level, injuries, or other relevant health factors.

To enhance motivation and adherence to the eight-week neuromuscular-cognitive training program, each female volleyball player will set an individualized goal based on her personal objectives. These goals will be used to enhance engagement without altering the standardized exercise prescription. A simple checklist will be provided to each participant to track progress, monitor ongoing performance, and record the frequency and type of cognitive and neuromuscular errors, encouraging motivation through ongoing personalized feedback. To avoid mental fatigue and maintain engagement, the protocol includes varied neuromuscular and cognitive training components. Team coaches will actively participate in delivering the training, guiding sessions, and ensuring high-quality execution.

During the intervention period, participants will be instructed to avoid performance-enhancing stimulants, tobacco, non-steroidal anti-inflammatory drugs (NSAIDs), or other analgesics within 24 hours before each training session to minimize potential effects on pain perception and physical performance. They will be permitted to continue their regular team training sessions and maintain their usual physical activity and dietary habits throughout the study.

### Timeline

The study timeline and schematic overview, including participant enrolment procedures, baseline and post-intervention outcome assessments, and the eight-week intervention period, are presented in Fig 1.

**Fig 1 pone.0353944.g001:**
[figure not shown]
Schedule of enrolment, interventions, and assessments. − t_1_, enrolment and screening week; t_0_, allocation and baseline assessment; t_1_ - t_3_, interventions; t_4_, post-interventions assessment.

### Outcomes

Participants will first receive detailed information about the study procedures, ethical considerations, and potential risks before providing informed consent and completing a personal information form. They will then undergo standardized instructions and a familiarization session, followed by a warm-up to standardize physical readiness and minimize injury risk. Assessments will be conducted 72 hours before the start of the eight-week neuromuscular-cognitive training protocol (pre-test) and within 72 hours after the final session (post-test) to evaluate its effects on modifiable ACL injury-related risk factors in female volleyball players with DKV. All assessments will take place in the Sports Rehabilitation Laboratory at Bu-Ali Sina University under standardized temporal and environmental conditions, with precise measures to control external variables and ensure accurate evaluation.

The primary outcome is the change in two-dimensional landing kinematics, particularly movement patterns associated with DKV, during single-leg landing under two conditions: with and without a concurrent cognitive task. Secondary outcomes include electrocortical brain activity measured by electroencephalography (EEG), lower limb muscle activity assessed by surface electromyography (sEMG), single-leg balance, lower limb muscle strength, and knee joint proprioception. These measures will determine the intervention’s impact on neuromuscular, cognitive, and biomechanical factors associated with ACL injury risk.

### Harms

All self-reported adverse events, unintended intervention effects, or changes in participants’ health status, including pain, discomfort, musculoskeletal symptoms, or injuries, will be documented and reported to the principal investigator for review and appropriate action.

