### Maintenance strategy

Several strategies will be used to minimize participant dropout. A study coordinator will send reminder text messages before each scheduled training and assessment session. Training sessions will be embedded within each team’s existing practice schedule to minimize scheduling conflicts with competitions and academic commitments. Where feasible, makeup sessions will be offered for absences due to illness or minor scheduling conflicts, provided the participant does not meet the withdrawal threshold defined in the Exclusion Criteria. Reasons for dropout or withdrawal will be systematically recorded and reported using a CONSORT flow diagram. Participants who complete the full protocol will receive individualized feedback on their landing mechanics as a non-monetary incentive to continue engaging.

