### Theoretical framework and design principles

This intervention protocol was developed based on the seven-step JUMP-ACL framework, incorporating evidence-based neuromuscular and cognitive training principles [18–20]. The intervention aims to address modifiable neuromuscular and biomechanical risk factors associated with ACL injury in young female volleyball athletes through a structured, progressive eight-week program. Previous literature has suggested that female volleyball athletes demonstrating DKV patterns may exhibit altered lower-extremity biomechanics associated with increased ACL loading during high-demand athletic tasks. Accordingly, the intervention is designed to improve movement mechanics and enhance lower-limb neuromuscular control under cognitively demanding conditions that approximate the attentional demands of real-game scenarios.

Based on previous literature regarding barriers to injury prevention program implementation in team sports and practical considerations identified through consultation with volleyball coaches, potential barriers to adherence include limited awareness of injury prevention strategies, time constraints within training schedules, and limited coach training in neuromuscular-cognitive intervention delivery. To address these barriers, the current protocol incorporates several implementation strategies, including comprehensive coach education, integration of training within existing team schedules, provision of detailed instructional materials, and emphasis on the cognitive training component to enhance athlete motivation and engagement.

Before intervention commencement, a two-hour standardized training workshop will be conducted for all participating team coaches and assistant coaches. The workshop will cover ACL injury mechanisms and prevention strategies, neuromuscular and cognitive contributors to injury risk in female athletes, demonstration and hands-on practice of intervention exercises, administration of cognitive tasks and integration of dual-task conditions, use of standardized performance evaluation checklists, identification of movement and cognitive errors, safety procedures, injury management and communication protocols, and strategies to maintain athlete motivation and adherence.

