All exercises in the program follow four core principles to ensure effectiveness and safety. The first is progressive overload, involving gradual increases in difficulty from simple to complex movements, single-task to dual-task conditions, and stable to less stable conditions when appropriate. The second is variety, as a wide range of exercises is included to maintain athlete engagement and target multiple performance aspects, such as strength, balance, power, and coordination. The third is repetition and continuity, ensuring sufficient practice volume and consistency to reinforce motor learning and potentially facilitate neural adaptations related to motor control. Lastly, expert supervision is essential, with trained staff consistently monitoring exercise execution to ensure proper technique, reduce inappropriate movement strategies, and provide immediate feedback and correction.

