### Intervention protocol

The intervention will be conducted over eight consecutive weeks, with three supervised training sessions per week, each lasting 60 minutes (a total of 24 supervised sessions). These will be scheduled within the teams’ regular training times to minimize disruption and enhance adherence. Sessions will be performed on non-consecutive days to allow adequate recovery. Each session will follow a standardized structure: Warm-up (15 minutes), including dynamic stretching, light aerobic activity, and sport-specific movements according to established protocols; main training (30–40 minutes), focusing on progressive neuromuscular and cognitive exercises; and cool-down (10 minutes), consisting of static stretching of the primary lower-extremity muscles and breathing exercises to facilitate recovery.

The intervention was structured as a four-phase progressive training protocol, consisting of consecutive two-week stages with specific objectives and gradual increases in motor complexity and cognitive demands (Tables 1 and 2).

**Table 1 pone.0353944.t001:** Categorization of exercises based on movement plane, limb involvement, and equipment use.

*Exercise Name*	*Sagittal (S)*	*Frontal (F)*	*Transverse (T)*	*Double Leg*	*Single Leg*	*Equipment*

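### Harms rest on athlete self-report with no scheduled question in either arm, so mild pain and injury are likely to be under-recorded; one fixed item on the existing post-session rating would mend this cheaply

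*Protocol article*

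**What the plan says.** The Harms section of the protocol article is one sentence. It covers "All self-reported adverse events, unintended intervention effects" and altered health, with pain and injury given as examples; these are to be written down and passed to the principal investigator, who decides on action. It names no question, form, time window or grading.

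Other sections bear on the point:

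- Control group protocol: participants in both arms are instructed to "report any changes in activity level, injuries, or other relevant health factors".
- Maintenance strategy: reasons for dropout or withdrawal are recorded and shown in the flow diagram.
- Intervention protocol (load monitoring): "Approximately 30 minutes after each session, each participant will rate her perceived exertion using the modified Borg CR-10 scale". No pain or injury item is mentioned.
- Intervention components: supervision means "trained staff consistently monitoring exercise execution to ensure proper technique".
- Theoretical framework and design principles: the coach workshop covers "safety procedures, injury management and communication protocols".
- Implementation: trainers cannot be blinded. Assignment of interventions: Blinding states that participants and assessors are.

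**The concern.** Athletes are enrolled because they show dynamic knee valgus, and the last training phase is run at high intensity, under fatigue and time pressure. The Background argues that cognitive load can worsen landing faults of this kind, and cognitive load is the only planned difference between the arms. Whether dual-task training brings more pain or injury is therefore the natural safety question of this trial.

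The stated collection method leaves it to the athlete to come forward. Self-report without a prompt tends to pick up events that interrupt play and to lose the milder ones. If recording is incomplete, the counts are too low. If it is incomplete to a different degree in the two arms, the comparison is distorted as well. The Discussion hopes that the program's feasibility may support later implementation, so a short list of events could be taken as reassurance that it does not give.

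**Working it through.** **What each provision can capture.** The provisions were compared on one question: does any of them ask every athlete about harms at a set time?

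- Harms: self-report, no set time.
- Control group protocol: a general instruction to report. The athlete still has to start the report, and pain is not named.
- Maintenance strategy: catches only a harm that ends participation.
- Supervision and coach workshop: concern technique and injury management. Neither is described as a step that records harms.
- SF-12 before and after (Data collection methods): a general quality-of-life score, not an event record.
- Post-session rating: asks every athlete at a set time, but about exertion only.

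None of them is a scheduled harms question.

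**How many contacts already exist.** The plan's session count reproduces: 8 weeks × 3 per week = 24. With 30 athletes allocated 1:1, that is at most 15 × 24 = 360 ratings per arm and 30 × 24 = 720 in all. These are maxima, since ratings are given only at attended sessions and the missed-session rule removes some athletes early.

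**What equal under-recording would do.** The protocol gives no event rates and no recording fractions, so the following are assumptions: true risks of 10% and 30%, and a share c of events recorded, the same in both arms. Observed risks are then c × 10% and c × 30%. Power is for a two-sided Fisher test at 0.05, by enumeration. The 12-per-arm column applies the protocol's 20% attrition (15 × 0.8 = 12).

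| Share recorded c | Observed risks | Risk ratio | Difference | Power, 15 per arm | Power, 12 per arm |
|---|---|---|---|---|---|
| 100% | 10% vs 30% | 3.0 | 20 points | 15% | 10% |
| 70% | 7% vs 21% | 3.0 | 14 points | 7% | 4% |
| 50% | 5% vs 15% | 3.0 | 10 points | 3% | 1% |

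With assumed risks of 20% and 50%, power at 15 per arm is 25%, 15% and 9% for the same three values of c. Equal under-recording lowers counts and power but leaves the risk ratio unchanged.

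**What unequal under-recording would do.** Assume a true risk of 30% in both arms, with 70% of events recorded in one and 50% in the other. The observed risk ratio is (0.30 × 0.50) / (0.30 × 0.70) = 0.15 / 0.21 = 0.71, where the truth is 1.

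**What sample size alone would do.** With no events among n athletes, the one-sided 95% upper limit is 1 − 0.05^(1/n): 18% for n = 15 and 22% for n = 12. This limit applies under any collection method, and a better question does not change it.

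**The case against.** The strongest reply is that self-reported does not mean unsolicited. Pain is self-reported however it is elicited, and Harms does not say that reports must be spontaneous. The instruction to report applies to both arms, withdrawal reasons are recorded, reports go to the principal investigator with no coach named as intermediary, and safety is not a listed outcome. A journal article may also condense a fuller harms procedure, and the Fig 1 schedule could not be read for this check.

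Much of this stands, and it rules out three stronger readings that a reader might infer:

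- *Harms are counted only if an athlete volunteers them.* The reporting instruction and the withdrawal record show that this goes too far.
- *The arms cannot be compared on safety.* The stated method is the same in both arms, and equal under-recording leaves the risk ratio intact. Distortion needs differential reporting. Unblinded trainers make that possible, but the document does not show that it will occur.
- *Athletes have a motive to conceal injury.* The missed-session rule and the completer incentive ("Participants who complete the full protocol will receive individualized feedback on their landing mechanics") may add some pressure. No passage penalises reporting, however, and makeup sessions are offered for illness or minor scheduling conflicts. Any effect on team selection is conjecture.

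The reply does not supply a scheduled question. The article states its harms method in the Harms section, and every channel it describes either waits for the athlete to report or catches only withdrawals.

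**Conclusion.** The point holds as a cheap improvement to the design, not as an error or a contradiction. Harms collection rests on self-report, a general instruction to report and recorded withdrawal reasons, with no standard question at a fixed time in either arm. That mild pain and injury will be under-recorded is a reasonable expectation, but its size cannot be derived from the document. The recording shares of 50% and 70% and the event risks used above are assumptions that show direction and scale only.

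Any between-arm comparison of harms is weak mainly because there are 15 athletes per arm. Incomplete recording weakens it further, and unblinded trainers leave it open to differential reporting. A low or equal count should not be read as evidence of safety.

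**What to change.** In Harms, keep self-report and add one fixed question on new pain, injury or symptoms since the last contact. It should record the site, any time lost, and whether the event arose in a study session or in other volleyball. Ask it in the same words in both arms, with the existing exertion rating at each attended session and again at the post-test.

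Send the answers to the principal investigator, as Harms already provides. They should not pass through the coach, who knows the arm. Nor should they go to the outcome assessors or the study coordinator, both stated as blinded: the arms train on separate days, so dated session forms could reveal allocation. A form that the athlete completes herself would also respect the instruction not to disclose intervention-related information during evaluations.

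Report events by arm, with the statement that 15 per arm cannot establish safety.

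The cost is one short item on a rating already collected, with no new visit. The downside is that more minor events will be recorded and reported. No change to progression or any other clinical rule is proposed.
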